# **PAPER-IV**

Effect of Pelvic Floor Muscle Training to improve Prolapse-Quality of Life in Sidama National Regional State, Ethiopia, 2022.

## Objectives

1. To Evaluate the Effect of Pelvic Floor Muscle Training on Prolapse-Quality of Life in Sidama Region, Ethiopia

## Study Area and Period

The same as for paper III

## Study Design, Study Subjects, Randomization, Sampling Technique and Description of Intervention

The same as for paper III

## Sample Size Determination

This sample size was based on paper III since we were unable to determine the effect of pelvic floor muscle training (PFMT) on quality of life as measured by the Prolapse Quality of Life Questionnaire.

## Data Collection Tools and Procedures

Data about health-related quality of life among patients with POP will be measured using the disease-specific tool called Prolapse-Quality of Life (P-QoL) (33). It was initially developed in 2005 to measure the severity of prolapse symptoms, its impact on patients’ health-related quality of life, and treatment outcome among English-speaking women. It is prolapse specific, a multidimensional tool with nine domains and 20 items. The domains include general health perception (GHP), prolapse impact (PI), role (RL), physical limitation (PL), social limitation (SL), personal relationship (PR), emotional disturbance (EMO), sleep/energy disturbance (SE), and severity measures (SM). Each domain has its own items/questionnaire each containing four points (0= none/not at all, 1= slightly or little, 2= moderately, and 3= a lot). Each domain has a score of 0 to 100, a higher score indicating poor quality of life. This tool was translated to and validated in the Amharic version. The Amharic version had categorized the nine domains into three major components. These components include Physical (physical component/PC; which is composed of general health perception, prolapse impact, physical limitation, social limitation, role, and severity measure), psychological, which includes: emotional disturbance and sleep disturbance) and personal relationship (25). In the current study, the Amharic version will be used after being translated into Sidaamu Afoo and translated back to check for consistency.

In addition, after the intervention, to evaluate patients' overall satisfaction with their post-intervention conditions, Patient Global Impression-Index (PGI-I) tool (27, 34) will be used. This tool measures how patients perceive their improvement after intervention. It contains a single item of a seven-point scale (7=very much worse, 6=much worse, 5=minimally worse, 4 = no change, 3=minimally improved, 2=much improved, and 1=very much improved). This score will be re-categorized as disease deterioration (minimally worse, much worse, or very much worse), no change (the same, remain stable), and disease improved (very much improved, improved, or minimally improved). This tool will be used after translated into the local language (Sidaamu Afoo) and back to English to check for consistency.

Data collection will be conducted in two phases. The baseline data will be collected from 130 symptomatic POP stage I-III participants at the health facility immediately as soon as they are diagnosed with POP (Paper-II). The data will be collected through face-to-face interviews by the same person who perform pelvic examination from 01 June – 24 July 2022. The end-line data will be collected after six months of intervention. The data will be collected at the household level by data collectors who know the house of these participants. These data collectors will be those who collected the data at the beginning of the study (Paper-II).

## Variables

The primary outcome variable of this study is a change in Health-Related Quality of Life (HRQL). The secondary outcome is participants’ perceived change in Prolapse impact on their quality of life measured by Patient Global Impression of Improvement (PGI-I) (34). The intervention is Pelvic Floor Muscle Training and other covariates include degree of POP, the severity of POP-SS, adherence to Pelvic Floor Muscle Training protocol, maternal age, location of POP (anterior, posterior or apical), number of childbirth, level of education, history of depression, need for fertility, body mass index, trauma, marital status, occupation, age at first delivery, place of delivery, history of prolonged labor, medical problem (chronic cough, diabetes mellitus), family history of POP, mode of delivery.

## Data Measurements

Study participants’ adherence to training protocol will be evaluated at each follow-up time (week 2, 6, 10, and 15). At week two, women will be assessed for adherence to pelvic floor muscle exercise in the last two weeks (a few days per week, once per week, a few times a week, once a day, three times a day). At weeks six, 10, and 15, they will be assessed for adherence to pelvic floor muscle exercise in the last four weeks using similar questions used on week two (a few days per week, once per week, a few times a week, once a day, three times a day). In addition, they will be assessed for improvement in prolapse quality of life at 10 and 15 weeks. At the end of six months, the overall adherence to training protocol will be evaluated from their dairy or report of pelvic muscle trainer. Women’s adherence to training protocol is considered adequate when they complete at least 80% of the training sessions (24).

Prolapse quality of life will be measured for each three components of the tool separately. Each component will have a score of zero (0) to 100. The mean change of each component will be evaluated at the end of six months for both arms. The mean change will be compared between the two groups (intervention and control groups) to measure the effect of Pelvic Muscle Training. The secondary outcome, women’s perceived improvement after the intervention will be measured as improved, the same, or worsened based on Patient Global Impression of Improvement (PGI-I).

## Quality Assurance

The same as for paper III. However, the P-QoL tool will be translated but not validated in Sidaamu Afoo.

## Data Management and Analysis

The Data management and analysis procedure is similar with paper-III. In addition to that, a paired t-test will be used to evaluate the mean change of the three components of P-QoL from baseline for both groups (intervention and control) groups. Then an independent t-test will be used to compare the mean change for interventional groups against the mean change of the control group as the effect size for all the three components separately. The level of significance will be set at a P-value < 0.0125 by using the Bonferroni correction formula for multiple outcomes (16, 29, 30).

## Ethical Considerations

This study protocol will undergo review by the Institutional Review Board of Hawassa University at the College of Medicine and Health Sciences. Once it is approved, a support letter will be obtained from Hawassa University College of Medicine and Health Sciences and given to the Sidama National Regional Health Bureau for permission and co-operation. A support and permission letter obtained from Sidama National Regional Health Bureau will be submitted to Dale district and Wonsho district Health Offices. A letter from the district Health Offices will be submitted to their respective health facilities and Kebele administrative included in the study.

To reduce the risk of stigma and discrimination, the baseline data will be collected in a private space (location) at the home of the participants. The leading data collectors will be female data collectors who are fluent in the local language, Sidaamu Afoo, in which the data will be collected. These data collectors will introduce the objective of the study, the data collection process, and how to ensure the privacy and confidentiality of the participants. Finally, written consent will be obtained. Those who cannot read and write can sign their names with their index fingers, stating that the consent was read to them by data collectors. Pelvic examinations will be performed at delivery rooms or gynecology outpatient departments and the physical privacy of participants will be ensured. Similarly, both lifestyle counseling and pelvic floor muscle training will be provided in a private room.

All study information will be confidential. Upon enrolment, subjects will be assigned a code that will be used instead of their name or other personally-identifying information. The key associated with the codes and the subjects’ personally identifying information will be restricted to the principal investigator and study staff. Once the data is collected and entered into the Epidata version 3.1 software, all information will be de-identified and the data analysis will contain only the subject code. All hard study tools will be stored in a locked cabinet with restricted access to others, and it will be controlled by the study investigator. The electronic data will be stored in STATA version 16 software for five years.

The risks to participants in this study are minimal. All questionnaires and study tools are designed in the local language so that participants can easily understand them. There is a small risk of psychological distress in exposing their private organs for a pelvic examination. There is also a risk of temporary discomfort associated with the physical exam performed at each study visit. Moreover, there is a risk of inconvenience related to returning home for follow-up visits. These risks will be minimized during the consent process by allowing participants to cease enrolment at any time. The travel cost and time compensation will be covered by the research team (200 Ethiopian Birr, equivalent to four dollars on average). If the participant cannot attend follow-up visits, the trainer will visit her at home.

Participants with advanced stages of prolapse (stage-IV) will be linked to the Yirgalem Hamlin Fistula Center for further management if the participant is a volunteer. The risks associated with pelvic floor muscle training are not yet reported, so this intervention will not add risk to these subjects

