The demand for conservative management is common especially for women giving birth at an older age ([109](#_ENREF_109)). Moreover, currently, the most important outcome of POP treatment is health-related quality of life and patient satisfaction ([14](#_ENREF_14), [112](#_ENREF_112)). POP causes a vaginal bulge, voiding dysfunction, and sexual dysfunction which adversely affects the quality of life ([9](#_ENREF_9), [14](#_ENREF_14)). Sexual function is complex and may not be managed with surgery for POP. The relationship status and sexual desire might not improve by structural change (surgery) ([31](#_ENREF_31)).

If the result of the current study is effective in improving prolapse symptoms and quality of life, the intervention will be expanded to wider areas. Therefore, evaluating the effectiveness of this non-surgical, cheap and no side effect treatment option has important value to improve women's health. This study will also reveal how much women’s health-related quality of life is affected by prolapse symptoms. This in turn will contribute to enabling the family and community to understand and help women with pelvic organ prolapse. The long-term goal of this study is to produce knowledge used to improve health care for women with Pelvic Organ Prolapse in Sidama National Regional State, Ethiopia.

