## Data Measurements

At each visit, women's adherence to pelvic floor muscle training will be evaluated by their pelvic muscle trainer. At week two, women will be assessed for adherence to pelvic floor muscle exercise in the last two weeks (three times a day, once a day, a more than once per week, once per week, a more than one days per week). At weeks six, 10, and 15, they will be assessed for adherence to pelvic floor muscle exercise in the last four weeks using similar questions used on week two (three times a day, once a day, a more than once per week, once per week, a more than one day per week). In addition, they will be assessed for prolapse symptoms at weeks 10 and 15.

At the end of six months, the overall adherence to training protocol will be evaluated from their dairy or report of pelvic muscle trainer. Women’s adherence to training protocol is considered adequate when they complete at least 80% of the training sessions (24). This will be calculated at each visit based on the training session and finally compiled.

The primary outcome of the study is a change in prolapse symptoms measured by POP-SS. The POP-SS is the same measurement with study one which measures the frequency of prolapse symptoms in the last four weeks, measured by seven items with a Likert-scale of 0 to 4 scale (0= never felt symptom, 1= occasionally, 2= sometimes, 3= most of the time and 4= all of the time). The total score will be calculated by summing up all responses for the seven-question and the total score will range from 0 to 28, the highest value indicating the severity of prolapse symptoms (25, 26). At the end of the six months, the mean change in prolapse symptoms from the initial visit will be compared between the two groups (intervention and control groups) to measure the effect of pelvic muscle training.

The secondary outcome, women’s perceived change in prolapse symptom since the start of the intervention, will be measured as improved, the same, or worsened based on Patient Global Impression of Change (PGIC) (14, 27).

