# **EXPECTED OUTCOME**

This study will have different outcomes. The first paper will produce a translated and validated Sidaamu Afoo version of the POP-SS tool that will be used to screen for disorder in this community. The second paper will determine and show the prevalence of POP and its risk factors in the community of the Sidama region. The effect and feasibility of pelvic floor muscle training in this specific study area will be evaluated. The training is expected to reduce the burden of prolapse symptoms and improve the quality of life among POP cases. If the training is effective in reducing prolapse symptoms and improving quality of life, it will be expanded to other areas. It is expected to reduce the cost of surgical POP management.

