**Bladder**:

- Instead of going to the bathroom 'just in case,' go when your bladder needs to be emptied
- Sit fully on the toilet, rather than hovering; this will aid in the relaxation of the correct muscles.
- You might find it beneficial to lean forward and back numerous times after passing urine to help make sure that all the urine comes out
- do not push or strain to empty your bladder; you might increase the prolapse
- Try not to lower your daily fluids (1.5 – 2 liters per day is recommended); you may aggravate the prolapse if you push or strain to empty your bladder.
- The number of times you need to empty your bladder may not always be reduced by drinking less.

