**Pelvic Floor Muscle Exercises**

Aim for 10 long squeezes, each held for 10 seconds, followed by 10 short squeezes.

- - If you can only hold the squeeze for a short period, you may need to start with ‘little and frequently’.
  - Perform pelvic floor muscle exercises at least three times per day.
  - When you are seated or lying down, you may find it easier to begin your routine.
  - Gradually increase your fitness program throughout the weeks and months.
  - After 3 to 5 months, you should notice a difference and should continue to practice your pelvic floor exercise once a day to keep the progress.
  - As your muscles strengthen, try doing your exercises in different positions, such as standing.
  - Eventually, you will be able to practice using these muscles while walking and bending.
  - Exercises for the pelvic floor muscles must be performed correctly.

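### The protocol says the training will not add risk, yet no visible part of the trial plan records adverse events or reasons for stopping the exercise

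*Protocol*

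**What the plan says.** Under Ethical Considerations (Paper IV) the protocol lists distress and discomfort from examination and the inconvenience of follow-up, and then says of the training itself: "The risks associated with pelvic floor muscle training are not yet reported, so this intervention will not add risk to these subjects". Section 2.7, Significance of the Study, takes the same position as a premise: "evaluating the effectiveness of this non-surgical, cheap and no side effect treatment option has important value".

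Expansion is tied to benefit only. If the result is favourable, "the intervention will be expanded to wider areas" (Significance of the Study). Expected Outcome repeats the intention: "If the training is effective in reducing prolapse symptoms and improving quality of life, it will be expanded to other areas". Neither place states a safety condition.

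For the training visits, Paper III (Data Measurements) says: "At each visit, women's adherence to pelvic floor muscle training will be evaluated by their pelvic muscle trainer". Prolapse symptoms are added at weeks 10 and 15, and Paper IV adds quality of life at the same weeks. The instruments named for six months are POP-SS and PGIC (Paper III) and P-QoL and PGI-I (Paper IV).

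**The concern.** The risk statement moves from an absence of reports to an absence of risk, and the second does not follow from the first. This would matter less if the trial then observed harms, because the statement could be checked. As planned, it does not. A positive trial would go forward as a case for wider use, accompanied by a safety claim that was assumed at the outset and never tested.

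**Working it through.** No figure in the protocol is in dispute, so the check sets its own sections side by side.

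**Step 1. What each source can register in the trial.**

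| Event | Where it could appear | Arms and time |
|---|---|---|
| New or worse bulge | POP-SS item on something coming down | Both, six months |
| Vaginal pain or discomfort | POP-SS item on vaginal discomfort or pain; P-QoL severity item | Both, six months |
| Perceived worsening overall | PGIC and PGI-I, categories 5 to 7 | Both, six months |
| Bleeding | No item | None |
| New urinary leakage | PFDI-20 and ICIQ-SF are in the survey questionnaire, but neither is named among the six-month tools | None at end-line |
| Care sought for a problem | No item | None |
| Stopping exercise because of a problem | Visits and diary record how often exercise was done, not why it stopped | None |

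The first three rows measure the target condition and serve as efficacy outcomes. The last four are not covered.

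**Step 2. How the data will be compared.** The Data Management and Analysis sections of Papers III and IV specify paired t-tests within arm, then independent t-tests of mean change between arms for POP-SS and the three P-QoL components, with a mixed model for adjustment. A mean improvement is compatible with some women getting worse, so these tests alone do not show worsening. PGIC and PGI-I do classify each woman as improved, the same or worsened, and are listed as secondary outcomes.

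**Step 3. Who is seen, and by whom.** The visits at weeks 0, 2, 6, 10 and 15 are described for the intervention group only. The six-month home interview covers both arms, and its interviewers are to be blinded. It is therefore the only planned contact at which events can be asked about equally.

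**Step 4. Set the claims against the data.** A statement that no risk is added needs at least a count of events by arm. Steps 1 and 2 show that the plan yields none beyond worsening of prolapse symptoms and quality of life.

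**The case against.** The strongest reply is that harm is not ignored. Both arms are asked at six months about bulge and vaginal pain, P-QoL asks about pain or discomfort due to the prolapse, and the two global impression scales already have a category for deterioration. This stands: it would be wrong to say that nothing bearing on harm is collected, and new items on bulge and vaginal pain would largely repeat existing ones.

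A second reply is that the trial has no safety objective, and that both statements sit in ethics and background text. That is also true, and it limits the weight of the point. It does not rescue the statements, which are made without qualification.

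A third is that details may be left to an analysis plan or to papers not shown. Tables may be. What women are asked, however, is fixed by the visit plan and questionnaire in the protocol. The information sheet (Annex I) was not available for this check and no trainer's visit form is among the annexes shown, so the finding covers visible material only.

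A reader might go further and infer that the protocol's own leaflet contradicts the safety claim. Annex IV does not support this. The line "do not push or strain to empty your bladder; you might increase the prolapse" is advice on passing urine, in the lifestyle part that precedes the intervention-only section. "Exercises for the pelvic floor muscles must be performed correctly" is a cue about technique, as are the remarks on tiring the muscles and not holding the breath. None says that the exercise causes harm, and the leaflet elsewhere says it can help to prevent worsening.

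**Conclusion.** The point holds in a limited form. The inference in Ethical Considerations is unsound, the description in Significance of the Study is unsupported, and the trial as written cannot support either one. The gap is specific: bleeding, new leakage at end-line, care sought, and stopping because of a problem.

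Its size cannot be put as a number. A reader might want to attach the upper confidence limit that zero events in one arm would give. That limit describes a hypothetical trial in which events were recorded and does not measure an error in this plan. Neither the primary estimate nor its validity is affected, and nothing in the documents suggests that the training is in fact harmful. This is a cheap improvement, resting on the assumption that no removed or separate form already collects these events.

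**What to change.** 1. In Ethical Considerations, replace the inference with a statement that no risk is known and that adverse events will be recorded in this trial. In Significance of the Study, delete the claim that the treatment has no side effects.
2. Add to the six-month interview, worded identically in both arms and without mention of the exercise so that interviewers stay blinded, items on bleeding, new leakage, any other new pelvic problem, and care sought.
3. At the training visits (intervention arm only), have the trainer record whether exercise was stopped because of a problem. This describes tolerability in the trained women and is not a comparison between arms.
4. Report by arm the number of women with any such event, with a POP-SS rise from baseline, and with PGIC 5 to 7.

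The cost is about four interview items, one entry on the trainer's record and one table, all at contacts already planned. The downsides are a slightly longer interview and a less favourable safety statement.

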## Trial Registration

Once the proposal is approved and ethical clearance is obtained, it will be registered at ClinicalTrials.gov ([Home - ClinicalTrials.gov](https://clinicaltrials.gov/)).

# **EXPECTED OUTCOME**

This study will have different outcomes. The first paper will produce a translated and validated Sidaamu Afoo version of the POP-SS tool that will be used to screen for disorder in this community. The second paper will determine and show the prevalence of POP and its risk factors in the community of the Sidama region. The effect and feasibility of pelvic floor muscle training in this specific study area will be evaluated. The training is expected to reduce the burden of prolapse symptoms and improve the quality of life among POP cases. If the training is effective in reducing prolapse symptoms and improving quality of life, it will be expanded to other areas. It is expected to reduce the cost of surgical POP management.

